### Ethics approval and consent to participate

The study was approved by the Institutional Review Board of Children’s Hospital of Philadelphia (CHOP, IRB#19–016865). Caregivers will be required to provide consent for their child to participate in the study, and students will be required to provide assent. A waiver of consent was obtained for the screening of student participants to obtain referrals and determine eligibility. Consent for the participation of teachers (who nominate students for participation and provide data on participating students) in this study will be indicated by their submitting referrals for students to participate in the study. Only authorized study staff will obtain consent from study participants. Plans to modify the study protocol must be reviewed and approved by the Institutional Review Board.

### Data analyses

#### Data collection and management.

Data from caregivers, teachers, providers, and students will be collected electronically using REDCap (Research Electronic Data Capture; [38]). All participants will be assigned a unique study ID number, which will allow for a deidentified dataset at the time of analysis. Prior to conducting the main statistical analyses, the distributions of continuous variables will be checked for normality and the presence of outliers. When there are substantial deviations from normality, an appropriate method of variable transformation will be selected (such as a log transformation for skewed variables). We will use independent samples t-tests, Wilcoxon Sign Rank Test, or chi-square tests to compare groups on pre-treatment demographic characteristics (e.g., student age and gender, family socioeconomic status) and scores on outcome measures. Variables for which there are statistically significant differences between groups will be included as covariates in subsequent analyses. Continuous variables will be characterized using means, medians, ranges, and standard deviations. Categorical variables will be characterized by frequencies and percentages. Summary tables will be created that present means and standard deviations for each assessment period (Baseline, Post-Treatment, 6-Month Follow-Up, 12-Month Follow-Up) for each intervention condition, as applicable.

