#### Concealment.

Given that the study is a pragmatic trial being conducted under real-world conditions, no attempt will be made to conceal treatment assignment from caregivers, students, teachers, and intervention providers. In addition, study team members will be fully aware of treatment assignment.

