### Student participants

Students will be eligible for this study if: (a) they attend a school participating in the study, (b) they are enrolled in grades 6–8 and placed in general education for a majority of the day, and (c) they are identified as having OTMP deficits that are impairing academic performance, as identified by the four interference items on the Children’s Organizational Skills Scale-Teacher version (COSS-T; [22]). Students classified with emotional/behavioral disorders and/or learning disabilities will be included if it is determined that the students’ disabilities are being addressed adequately in their current educational program and OTMP skill deficits are a primary concern. Students with a one-to-one aide will be excluded because the presence of an aide substantially alters how an organizational intervention is implemented. In addition, students from families in which both caregivers do *not* speak English will be excluded because the program has not yet been developed for non-English speakers. Parents or legal caregivers must give consent, and students must provide assent for student and family participation, which can be withdrawn at any time during study participation. The potential for harm to participants is minimal, but they are informed that it is possible they may feel uncomfortable in completing measures. Participants are not mandated to complete items on measures used in the study.

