### Outcome measures – Proximal and distal

The *Children’s Organizational Skills Scale – Parent and Teacher versions (COSS-P, COSS-T)* will be used to assess changes in OTMP functioning at home and school. COSS Total scores (26 items for COSS-P, 28 for COSS-T) have strong construct and discriminant validity [23] and treatment sensitivity [4]. Each item is rated on a 4-point scale. The total score will be used in analyses, with higher scores being less favorable.

The *Homework Problem Checklist (HPC)* is a 20-item caregiver-report measure that indicates the frequency of child homework problems. The HPC has been shown to have strong construct validity [24] and treatment sensitivity [4]. Each item is rated on a 4-point scale. The total score will be used in analyses with higher scores indicating more problems.

The *Homework Performance Questionnaire – Teacher version (HPQ-T)* assesses students’ homework behavior during the past 4 weeks. Each item is rated on a 7-point scale indicating how often each behavior occurs, with higher scores indicating better performance. The 17-item General factor that assesses overall homework competence has strong construct validity [25] and will be used in analyses.

The *Academic Proficiency Scale (APS)* is a teacher-report measure assessing proficiency in six academic subjects. Each item is rated on a 5-point scale (1 = well below standard expected at this time of year; 3=at standard; 5 = well above standard). This measure has high internal consistency [8] and strong treatment sensitivity [5]. The mean item score will be used in analyses, with higher scores indicating better performance.

Student *academic report card grades* will be used to examine the impact of HOPS vs. TAU/WL on academic performance. Student grades will be recorded for the last marking period of the year prior to enrollment (baseline), the year of enrollment (post-treatment), and the year following enrollment (follow-up). Grades will be harmonized across participating school districts to a uniform grading scale (ranging from a low of 1 to a high of 4). A composite academic grade score will be computed for each student based on their grades in math and reading/language arts (possible range = 1–4). Higher scores indicate better outcomes.

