#### Analyses for Aims 1–3: Evaluation of HOPS vs. TAU/WL and comparison of HOPS-ST to HOPS-RT.

*Hypothesis 1:* Students in HOPS-ST will demonstrate significantly fewer OTMP skills deficits and homework problems and will show significantly better academic performance at post-treatment compared to students in TAU-WL*Hypothesis 2:* Students in HOPS-RT will demonstrate significantly fewer OTMP skills deficits and homework problems and will show significantly better academic performance at post-treatment compared to students in TAU-WL.*Exploratory:* Examine whether the effects of HOPS-ST and HOPS-RT differ at post-treatment and follow-up.

A linear mixed-effects modeling approach will be used to examine intervention effects at post-treatment. An intent-to-treat approach to data analysis will be applied, including all children with baseline data in the analytic model. Under this approach, we will examine differences between students in HOPS (for HOPS-ST and HOPS-RT separately) vs. TAU-WL (as well as for students in HOPS-ST vs. HOPS-RT) by fitting a multilevel model in which students are nested within schools. In addition to including an indicator variable for the treatment condition, we will include covariates that explain variation at the student and school levels. To explore the sustainability of the intervention effect, we will examine how both means and slopes (rates of change) vary from baseline to 6-month and 12-month follow-up using regression analyses. Changes in mean and slope reflect variations in the magnitude of effect and pace of change during different phases of the study.

Because the efficacy of HOPS will be evaluated on three different domains of outcome measures (organizational skills, homework performance, academic achievement), we will use a Bonferroni-adjusted significance level to correct for multiple comparisons within each domain. As a result, the significance level will be adjusted to.025 per domain for the two measures of organizational skills (COSS-P, COSS-T), the two measures of homework performance (HPC, HPQ-T), and the two measures of academic achievement (APS, academic grades).

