Power calculations were based on the following design parameters: *N = 30* schools (20 assigned to HOPS, 10 assigned to TAU); ICC = 0.04 (based on [4]); α=0.025  (reflecting the Bonferroni corrected significance level to accommodate multiple testing of two outcomes for each outcome domain); and $R^{\text{2}}=\text{0}.\text{6}\text{0}$ at the student and school level (which is the proportion of variation in outcomes explained by student and school-level covariates). Based on initial projections, we expected to enroll 8 students per school for a total of 240 participants (216 with 15% attrition), which would be sufficient to identify a minimal detectable effect size (MDES) of 0.41. Because of recruitment challenges primarily due to barriers related to the COVID-19 pandemic, we adjusted these projections to an average of 4.5 students/school for 30 schools for a total of 135 participants (122 with attrition). This sample size will result in a MDES of 0.48 with adequate power (80%). Based on prior research by [name] and colleagues [4], the MDES for primary outcomes in our study is well within the range of expected effect sizes.

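### Normality is checked on the variables before modelling rather than on model residuals, which leaves the primary outcome scale open to a choice made after an unblinded team has seen the data

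*Protocol article*

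**What the plan says.** Under Data collection and management, the protocol article states that, before the main analyses, "the distributions of continuous variables will be checked for normality and the presence of outliers". The consequence follows directly: "When there are substantial deviations from normality, an appropriate method of variable transformation will be selected (such as a log transformation for skewed variables". It gives no cut-off for what counts as substantial and no list of variables, and it offers the log only as an example. Residuals are not mentioned.

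Under Analyses for Aims 1–3 the primary method is fixed: "A linear mixed-effects modeling approach will be used to examine intervention effects at post-treatment", with students nested in schools and covariates at both levels. On multiplicity, "the significance level will be adjusted to.025 per domain", covering two outcomes in each of three domains.

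Under Outcome measures the analysis scales are already named. For the COSS, "The total score will be used in analyses, with higher scores being less favorable"; the HPC total, the APS mean item score and a 1–4 grade composite are likewise specified. Under Concealment, "study team members will be fully aware of treatment assignment".

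**The concern.** Two things are wrong with the stated rule.

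First, it inspects the wrong quantity. A linear mixed model makes its normality assumption about residuals and random effects. Covariates need no normality at all, and an outcome can be skewed simply because a strong covariate is skewed. A check made before any model is fitted cannot be a residual check.

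Second, it makes the primary outcome scale depend on the data, with the choice left to people who know the allocation. The text does not say that the check is pooled over arms or that the choice is made blind.

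At stake is mainly the estimand. This is a replication: Aim 2 sets HOPS-RT against the prior trial, and the power section says that "the MDES for primary outcomes in our study is well within the range of expected effect sizes", with the range taken from that trial. A log-scale coefficient is not on the COSS, HPC, HPQ-T, APS or grade scale, and it cannot be set directly beside the prior trial's d values.

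**Working it through.** The plan states no figure on this point, so there is none to reproduce. The check has three parts.

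**Inputs from the protocol article (power calculations):** 30 schools, 20 HOPS and 10 TAU; 122 students after attrition; ICC 0.04; R² 0.60; α 0.025, taken as two-sided because sidedness is not stated. **Assumptions:** the shape of the baseline score, the correlation between the selection score and the analysed score, and Shapiro–Wilk at 0.05 as a stand-in for the unstated criterion.

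**1. What a raw-outcome check responds to.** Standardize the outcome as y = √0.60·x + √0.40·e, with covariate part x independent of residual e. Then

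skew(y) = 0.60^1.5·skew(x) + 0.40^1.5·skew(e) = 0.465·skew(x) + 0.253·skew(e).

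Skewness in the covariates, which is harmless, gets 0.465/0.253 = 1.8 times the weight of skewness in the residuals, which is what matters. A residual skewness of 1 would show as only about 0.25 in the outcome if x is symmetric. So the check can fire without cause and can also miss a real problem.

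**2. How often it fires when the residuals are truly normal (n = 122, R² 0.60).**

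| Baseline of the analysed score | Raw post-treatment outcome flagged | Residuals flagged |
|---|---|---|
| Normal | 5% | 4% |
| Truncated directly at 0 or +1 SD | 45–66% | about 5% |
| Exponential (skewed) | 83% | about 5% |
| Selection on another score, correlation 0.9 | 11–13% | about 5% |
| Same, correlation 0.8 | 7–8% | about 5% |
| Same, correlation 0.7 or lower | about 5–6% | about 5% |

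A looser trigger of absolute skewness above 1, used only to illustrate a substantial deviation, flags the outcome in 1–6% of trials under direct truncation and in about 0% at correlation 0.8 or below.

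**3. Error rate and power (4,000 simulated trials, t-test on covariate-adjusted school means, all HOPS against TAU).**
- Always raw scale: type I error 0.028–0.029.
- Rule followed mechanically on pooled data: 0.026–0.028. The simulation standard error is √(0.025 × 0.975/4000) = 0.0025, so this does not differ from 0.025.
- Smaller p-value of raw and log taken freely: 0.033–0.036 here, and up to 0.038 in a separate run.
- True effect 0.48: an unneeded log of the outcome lowers power from 0.90 to 0.87–0.88. The loss of 0.02–0.03 is the point, not the level.

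The log can also be the wrong remedy. COSS and HPC totals are scored so that higher is worse. If scores bunch near the top they are left-skewed, and a log makes that worse.

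**The case against.** The strongest reply has four parts.

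**Selection does not truncate the outcomes.** A reader might infer that, because students qualify when "they are identified as having OTMP deficits that are impairing academic performance", baseline scores are cut off by design and the rule is bound to fire. The documents do not support this. Student participants names four COSS-T interference items as the basis. The analysed outcomes are the COSS-P and COSS-T totals, HPC, HPQ-T, APS and grades, and none is stated to be the selection score. Selection on a correlated score leaves flag rates near 5–13%. This part stands: the rule can fire, but the article does not show that it will.

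**The rule as written does not inflate type I error.** A reader might infer that a data-driven scale raises the error rate of the 0.025 tests. The check comes before the main analyses and is triggered by shape, not by the treatment effect. Followed mechanically, it stays at nominal. Inflation needs someone to compare treatment results on both scales and keep the better one, which the text does not propose. This also stands.

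**Raw-scale effects remain computable.** Means and SDs are to be tabulated by condition and time point. This stands in part: such an effect would be descriptive, not the covariate-adjusted primary estimate.

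**Cut-offs and diagnostics belong in a SAP.** That answers the missing threshold and variable list. It does not answer the main point, because the article does not leave the matter open: it states which quantity is checked and what follows.

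**Conclusion.** The point holds as a minor, easily corrected fault in a stated rule. The article checks variables where the mixed model calls for residuals, and it lets the primary scale be chosen after the data are seen by a team that is not blinded. It also sits badly with the article's own outcome section, which already names the scores to be analysed.

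The size is modest and mostly not about error rates. If the rule fires without need, the cost is an effect off the named scale, no direct comparison with the prior trial, and about 0.02–0.03 of power in the cases simulated. Type I error is near nominal under mechanical use and about 0.03–0.04 only under a free choice of scale. How often the rule would fire cannot be known from the documents. High rates need the analysed score itself to be truncated or strongly skewed.

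The conclusion assumes that the check is on unmodelled distributions, which is inferred from its timing and from the absence of any mention of residuals, and that no unseen SAP overrides it.

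**What to change.** Amend Data collection and management as follows:
- The six outcomes (COSS-P, COSS-T, HPC, HPQ-T, APS, grades) are analysed on their stated scales in the primary analysis.
- No outcome or covariate is transformed because of its raw distribution. Distribution checks before modelling serve description and data cleaning only.
- Normality is judged on the residuals of the fitted mixed model.
- If residuals are clearly non-normal, a bootstrap or small-sample cluster-robust interval is added. Any transformed-scale model is reported only as a labelled sensitivity analysis.

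This keeps the primary effect on the scales the article names and comparable with the prior trial, and it removes a discretionary choice. The cost is a change of wording and at most one extra sensitivity analysis; design, sample size and data collection are untouched.

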## Materials and methods

### Trial design

#### Random assignment to study conditions and providers.

The study is a two-group, parallel randomized controlled trial that is designed to include about 30 schools. Random assignment will be conducted at the level of schools and will occur after the school grants approval and the school provider offers consent. The study has two arms: HOPS and TAU-WL. Schools will be stratified by subsidized lunch status (low, medium, high) and randomly assigned to HOPS or TAU-WL at a 2:1 ratio. The sequence of assignments to treatment conditions will be determined using a computer-generated list of random identification numbers, conducted by the study statistician to ensure an unbiased and unpredictable assignment of participants to the study arms. The list of random numbers is generated using the statistical software program R [21]. The study team will inform the principal and school provider after random assignment of the school to study condition has been made. The study is designed to compare HOPS to what students typically receive to address their OTMP skills deficits. A WL design was chosen to be responsive to feedback from school officials who expressed concerns about participating in the study if identified students were not able to obtain HOPS. Students in TAU/WL schools will receive HOPS later in the school year of enrollment or in the school year following the year of enrollment. Students enrolled in the highest grade level in the school (e.g., 8^th^ grade) will be enrolled in the first few months of the school year, so that there is enough time for them to receive HOPS before the end of the school year if their school is assigned to the TAU/WL condition. Students will be enrolled in this study during the period from 25/10/2021–28/02/2026.

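### Baseline covariates are chosen by significance test, and neither each outcome's baseline score nor the lunch-status stratum is fixed in the Aim 1–3 models

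*Protocol article*

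**What the plan says.** Three parts of the protocol article bear on covariates, and a fourth on the randomization.

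- **Data collection and management** sets out baseline testing: "We will use independent samples t-tests, Wilcoxon Sign Rank Test, or chi-square tests to compare groups on pre-treatment demographic characteristics". Baseline scores on the outcome measures are among the variables tested. The selection rule follows: "Variables for which there are statistically significant differences between groups will be included as covariates in subsequent analyses". No significance threshold is given, and the section does not say which groups are compared.
- **Analyses for Aims 1–3**, on the multilevel model with students nested in schools, says that besides the treatment indicator "we will include covariates that explain variation at the student and school levels". No covariate is named.
- **The power paragraph in the same section** takes R² = 0.60 at student and school level, "which is the proportion of variation in outcomes explained by student and school-level covariates", again without naming any. With 135 enrolled and 122 after attrition it gives an MDES of 0.48 at 80% power.
- **Random assignment to study conditions and providers**: "Schools will be stratified by subsidized lunch status (low, medium, high) and randomly assigned to HOPS or TAU-WL at a 2:1 ratio".

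**The concern.** A baseline significance test measures how surprising a difference would be under chance. It does not measure how strongly the variable predicts the outcome, which is the reason to adjust. A strong predictor that happens to be balanced, or moderately imbalanced, stays out; an irrelevant variable that crosses the threshold goes in. The model is then known only after the data are seen, and it may differ between outcomes and between the three contrasts (HOPS-ST vs TAU-WL, HOPS-RT vs TAU-WL, HOPS-ST vs HOPS-RT).

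Two technical faults sit beside this. The tests treat students as independent, although HOPS versus TAU-WL was randomized by school. And the signed-rank test compares paired measurements, so it cannot compare independent groups.

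Precision is at stake. The power statement needs covariates that explain 60% of outcome variance. The baseline value of the same outcome is the natural candidate, and the lunch stratum belongs in the model because it was used to randomize. The text guarantees neither.

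**Working it through.** **Inputs, all from the power paragraph unless noted.** 30 schools, 20 HOPS and 10 TAU; ICC 0.04; alpha 0.025, taken as two-sided because sidedness is not stated; R² 0.60; 122 students analysed; 1:1 split of HOPS students between provider types (section on assignment to school or research provider). The average is 122/30 = 4.07 students per school, so HOPS-ST has about 40.67 students (half of those in 20 schools) and TAU-WL about 40.67 (all of those in 10 schools).

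**Step 1: reproduce the plan's MDES.**

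MDES = (t₀.₉₈₇₅ + t₀.₈₀) × √{(1 − R²)[ICC(1/J_T + 1/J_C) + (1 − ICC)(1/N_T + 1/N_C)]}, with 28 df.

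- Multiplier: 2.368 + 0.855 = 3.223.
- Bracket: 0.04 × (1/20 + 1/10) + 0.96 × (2/40.67) = 0.0060 + 0.0472 = 0.0532.
- With R² = 0.60: SE = √(0.40 × 0.0532) = 0.146, and MDES = 3.223 × 0.146 = **0.470**.

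With 115 analysed (15% attrition from 135) the MDES is 0.483. The stated 0.48 is therefore reproduced for a single-provider contrast. All HOPS versus TAU-WL gives 0.415 with 122 analysed.

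**Step 2: vary R².** Same contrast, 122 analysed, power at 0.48 from the noncentral t:

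| R² | MDES | Power at 0.48 |
|---|---|---|
| 0.60 | 0.470 | 82% |
| 0.50 | 0.526 | 72% |
| 0.40 | 0.576 | 63% |
| 0.30 | 0.622 | 55% |
| 0.20 | 0.665 | 49% |
| 0 | 0.744 | 40% |

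**Step 3: the significance rule acting alone (worst case).** Simulation with clustering: 20 HOPS schools with 2 HOPS-ST students each, 10 TAU-WL schools with 4 each, and one baseline score with R² = 0.60, kept only if its student-level t-test has p < 0.05. The 0.05 is an assumption. There were 6,000 trials per setting.

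| Adjustment | Power at 0.48 | Type I error (nominal 0.025) |
|---|---|---|
| Always | 81% | 0.021 |
| Never | 39% | 0.020 |
| Only if significant | about 40% | 0.010 |

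The score was selected in about 6% of trials, so the rule performs almost like no adjustment.

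**Step 4: what one sample can look like.** With 41 students per group and clustering ignored, a baseline difference of 0.30 SD gives t = 0.30/√(2/41) = 1.36, p = 0.18. At a 0.05 threshold the rule would not adjust. If the baseline–outcome correlation is √0.60 = 0.77, the unadjusted estimate in that sample is shifted by 0.30 × 0.77 = 0.23 SD, about half of 0.48.

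**Step 5: the rule as an addition to a fixed baseline score (mild case).** With 41 per group, clustering ignored, the baseline score always in the model and the p < 0.05 rule applied to 10 non-prognostic variables, power was 85.4% against 87.0% without the rule. Type I error was 0.026 in both.

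**The case against.** The best defence is that the significance rule is not the only way into the model. The Aims 1–3 section commits, without condition and without a p-value, to covariates that explain variation, and the R² definition in the power paragraph echoes that wording. On this reading the rule only adds imbalanced variables to a model that is already prognostic, and step 5 shows that this costs about 1.5 points of power. A condensed article may also leave the covariate list to a full protocol or SAP that is not shown.

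Much of this stands. A reader might infer that adjustment rests on p-values in place of the baseline score, or that the trial's power is in effect halved. The document supports neither. It does not say that the significance rule alone governs, nor which covariates are meant to supply R² = 0.60; that the baseline score supplies it is a plausible inference. A reader might also call the 0.23 SD in step 4 bias. It is a shift in one imbalanced sample and does not bias the estimator over repeated randomizations. The rule-alone error rate is conservative, so step 3 shows no inflation of false positives.

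It can also be said that imbalance need not be pure chance here: students are referred after schools are randomized and informed, and allocation is not concealed. That is a reason to attend to baseline differences, but adjustment that is always applied does so better than a test with little power.

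The defence does not remove the rule itself. It is written into the article as an instruction for later analyses, so it is not a detail left to another document, and the Aims 1–3 wording does not withdraw it. The signed-rank error is also on the page.

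**Conclusion.** The concern holds in a limited form and should be fixed. The article prescribes a significance-driven choice of covariates for a randomized trial, uses student-level tests where schools were randomized, and names a paired test for independent groups. It does not fix each outcome's baseline value or the lunch-status stratum, although its MDES depends on strong covariates.

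The cost depends on which reading of the text is applied. It runs from about 1.5 points of power, if the rule only adds to a model that already holds the baseline score, to a fall from about 81% to about 40% at 0.48 SD, if the rule alone decides entry of that score. These figures assume two-sided alpha 0.025, ICC 0.04, the HOPS-ST versus TAU-WL contrast with about 80 students in the clustered calculations, a 0.05 selection threshold and, in the simulations, a single baseline score carrying R² = 0.60. The mild-case figure also ignores clustering.

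**What to change.** 1. Delete the sentence that makes baseline significance the criterion for covariates.
2. State that every Aim 1–3 model includes the baseline value of the outcome analysed and the school lunch-status stratum (low, medium, high), whatever the observed balance. Grade level is optional. Name any other covariates in advance.
3. Say which of these covariates are expected to supply R² = 0.60.
4. Present baseline characteristics descriptively by group, without tests, and drop the signed-rank test.

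The cost is wording and a few degrees of freedom. Baseline outcome scores and school lunch percentages are already collected, baseline grades come from the year before enrolment, and the Missing data section already provides full information maximum likelihood for missing covariates. The change should be made before outcome data are analysed.
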